|         | 
taken (Treece & Treece, 1982). Based on results from a previous motor imagery training study using physiological measurements (mean and standard deviation of heart rate differences between groups), the sample size of 63 participants per group was obtained using the HyLown sample size calculation software (http://powerandsamplesize.com/). Since there will be three groups in this study, it was determined that 189 participants were needed for a full-scale study. Based on these recommendations in the literature, it was decided that the sample size for this pilot study should be 15 participants per group. The total sample size was planned as 54 participants (18 per group), with the addition of possible losses of 20%.
 
Randomization
 
Participants will be divided into three groups using a simple randomization method based on a single sequence using computer software (https://www.randomizer.org/) by a researcher who will not be involved in evaluation and treatment (Altman & Bland, 1999).
 
Motor imagery training
 
DVDs containing motor imagery instructions will be given to the individuals participating in the motor imagery training. The same content will be made available for download online to participants (control) who wish to do so.
 
Group 1 will be trained in activating kinesthetic motor imagery. Scenarios in this motor visualization training will focus on exercises that require high effort (plank, boxing, jumping, crouching, push-up, etc.). In the motor imagery scenarios of the participants in Group 2, low intensity (relaxation) exercises (breathing exercises, stretching, body awareness exercises, etc.) will be included. Motor imagery training for both groups, 5 days a week, 17 minutes a day. It will be applied for 2 weeks (Schuster et al., 2011).
 |                                     |

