#### **Applicability (feasibility) of the methods**

The feasibility of the methods (safety, side effects, rate of participant acceptance of applications), the feasibility of a full-scale study (target sample size, dropout rate, participation in targeted sessions) will be examined. The rate of falling out of the study should not be more than 20% and the participation in the sessions should not be less than 70%.

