| C.3.9  | 
STATISTICAL ANALYSIS
 
SPSS (version 24.0, IBM Corporation, Armonk, NY, ABD) software will be used in all statistical analyzes. The statistical significance level will be considered as two-sided <math>p < 0.05</math>. The compliance of the data to normal distribution will be evaluated by examining the results of skewness and kurtosis and histograms in addition to the Shapiro-Wilk test results.
 
Intention-to-treat analysis will be performed for all participants with follow-up data, considering the groups they were originally assigned to. Descriptive statistics will be used to summarize initial demographic variables.
 
The significance of the difference between pre-and post-training data will be analyzed in the dependent group using the t-test / Wilcoxon signed-rank test in accordance with the given distribution characteristics. Bonferroni correction will be used where necessary. Two-factor mixed pattern analysis of variance (ANOVA) will be used to examine continuous variables such that groups are a factor between participants and time is a factor for participants. Effect sizes will be calculated as partial eta square values. When a meaningful result is obtained in the relevant analysis, the reason for the difference will be examined with appropriate post hoc correction methods.
 |

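### The analysis called intention-to-treat drops randomised participants without a second assessment; it is an available-case analysis by assigned group, open to bias in either direction if loss relates to outcome.

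*Protocol*

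**What the plan says.** Section C.3.9 (Statistical analysis) fixes both the name and the membership of the analysis set: "Intention-to-treat analysis will be performed for all participants with follow-up data, considering the groups they were originally assigned to". For the comparison between groups it states: "Two-factor mixed pattern analysis of variance (ANOVA) will be used to examine continuous variables", with group as the between-participant factor and time as the within-participant factor. Testing is two-sided at 0.05.

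On losses, the sample size text in C.3 first settles on 15 per group, then adds an allowance: "The total sample size was planned as 54 participants (18 per group"), "with the addition of possible losses of 20" per cent. The feasibility text in C.3.7 sets the same figure as a ceiling: "The rate of falling out of the study should not be more than 20" per cent.

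On burden, C.3 and C.3.8 give both training arms the same schedule of 17-minute home sessions, five days a week for two weeks. Controls receive no programme. Under C.3.8 participants in all arms are telephoned and reminded of the second evaluation.

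**The concern.** Intention-to-treat has two parts: analyse people in the arm to which they were randomised, and include everyone who was randomised. The sentence in C.3.9 keeps the first and gives up the second. The mixed ANOVA does not restore it, because a standard repeated-measures ANOVA uses only participants with both the pre- and the post-training value. The protocol itself fixes the set and its label, so this is not a detail left open for a separate analysis plan.

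The label matters because readers take intention-to-treat to mean that the protection of randomisation is intact. Here it is intact only if those who miss the second assessment resemble those who attend. Two arms are asked for ten home sessions and one arm for none, so the reasons for leaving may differ between trainees and controls. The pilot is also meant to inform the feasibility and target size of a full-scale study, so a distorted effect estimate could carry forward.

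**Working it through.** **Inputs from the protocol.** 15 evaluable per group; 18 per group and 54 in total planned; 20% loss in both the sample size and the feasibility criterion; two-sided 0.05. No loss rate by arm and no reason for loss is given. Everything below about who is lost is an assumption.

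**1. The plan's own figure.** 15 × (1 + 0.20) = 18 per group; 18 × 3 = 54. This reproduces.

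**2. How many the rule can remove.** 0.20 × 54 = 10.8, about 11, which leaves about 43 analysed. If loss were 20% in each arm, the two training arms would lose 0.20 × 36 = 7.2 between them. If all 10.8 losses fell on trainees, their loss rate would be 10.8 / 36 = 30%.

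**3. Illustration with a true effect.** Assume that a fraction d of a training arm is lost and would have shown no effect, that the rest gain 0.50 SD, and that control losses are random. The effect in all randomised is (1 − d) × 0.50; the available-case estimate is 0.50. The ratio is 1/(1 − d).

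| Loss d | All randomised | Available cases | Ratio |
|---|---|---|---|
| 5% | 0.475 SD | 0.50 SD | 1.05 |
| 10% | 0.45 SD | 0.50 SD | 1.11 |
| 20% | 0.40 SD | 0.50 SD | 1.25 |

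**4. Illustration with no true effect.** Assume that 20% of a training arm is lost, that the tendency to leave is correlated ρ with poor change, and that control loss is random. The mean change of those remaining is shifted by ρ × φ(z) / (1 − d), with z the 20th percentile of the standard normal. For d = 0.20 this is 0.35 × ρ. The type I error column comes from a simulation of two arms of 18, each losing 4 (18 × 0.20 = 3.6, rounded), with a t-test on change and 8,000 runs.

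| ρ | Spurious difference (formula) | Simulated type I error at nominal 5% |
|---|---|---|
| 0 (random) | 0 | 5.3% |
| 0.3 | 0.11 SD | 6.5% |
| 0.5 | 0.18 SD | 8.2% |
| 1.0 | 0.35 SD | 19.9% |

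If good responders leave instead, the same shifts appear with the opposite sign.

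**5. Which remedy moves the estimate.** I simulated step 3 at 20% loss unrelated to baseline, with pre-post correlations of 0.3, 0.5 and 0.8. A baseline-adjusted estimate (ANCOVA, which stands in for the baseline-constrained mixed model) stayed at about 0.50 SD. Giving the missing trainees the control-arm mean change brought it to about 0.40 SD. It does so because that rule matches the assumption made in step 3. A mixed model therefore corrects loss that baseline values explain, and nothing more.

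**The case against.** The sentence states its own limit: anyone who reads it to the end can see who is analysed. That is fair, and it makes this a mislabelled set, not a concealed one. The label is still wrong and is what a later report would carry.

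A reader might infer that this is a completer or per-protocol analysis. The document does not support that. Someone who skips or abandons the sessions but attends the second evaluation stays in the assigned arm, and nothing in C.3.8 withdraws such people; all are reminded to return.

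A reader might also infer that the rule inflates the training effect. That is not established. The rule applies to all three arms, and controls with no programme may also fail to return. Loss of good responders would understate an effect. The 25% in step 3 is simply 1/(1 − 0.20) under an assumed zero effect in everyone lost. The resting metabolic and respiratory outcomes in C.3.7 have no stated direction of improvement. The activating and relaxing arms share one schedule, so unequal burden gives no reason to expect differential loss between them.

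Finally, this is a two-week pilot in healthy volunteers. The 20% is a ceiling, actual loss may be lower, and the dropout rate is itself a feasibility outcome. This limits the likely size of the problem. It does not make the analysis intention-to-treat.

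**Conclusion.** The point holds as a wrong label and a restricted set, with bias as a possibility. At the loss the plan accepts, about 11 of 54 randomised participants could be left out of an analysis named intention-to-treat. That much follows from the text alone.

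The size and direction of any bias depend on reasons for loss that the document does not give. Random loss gives none. Under the stated assumptions, 20% loss from a training arm can turn 0.40 SD into 0.50 SD, or produce 0.11 to 0.35 SD where there is no effect; the reverse pattern of loss would bias the other way. The concern applies mainly to the comparisons of training with control.

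**What to change.** - Rename the set in C.3.9 *available cases, as randomised*, and define intention-to-treat as all randomised participants in their assigned arms.
- State that participants who stop training are still assessed at the second evaluation. The reminder calls largely serve this already; the text should make it explicit.
- Report loss to the second assessment by arm, with reasons where known, alongside the overall dropout rate.
- Fit a mixed model to the pre- and post-training values with the baseline mean constrained equal across arms. It uses every participant with a baseline value and is equivalent to ANCOVA when data are complete. Say plainly that it handles only loss explained by baseline.
- Add one sensitivity analysis that gives missing training-arm participants the control-arm change, preferably by multiple imputation so that the standard error is not understated. Of the analyses proposed here, only this one addresses loss related to unobserved response.

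The sample size does not change. The cost is a few sentences of protocol text, two further analyses, and possibly smaller reported effects. If only one change is made, it should be the label together with loss reported by arm.

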|     | 
Duhamel, 2001). Motor imagery can also be defined as implicit or explicit (de Vries et al., 2013). Explicit motor imagery is defined as a phenomenological experience in which the sense of movement is experienced consciously (de Vries et al., 2013). That is, the individual is aware that he is imagining movement. On the other hand, implicit motor imagery is defined as unconscious visualization of movement (de Vries et al., 2013). For example, when an individual looks at a photograph of a hand standing in a different position than normal, he unwittingly imagines his hand gestures moving the hand to the position he is used to and decides whether the hand in the photograph is right or left. Open and closed motor visualization describe different aspects of cognitive task and should not be considered as separate situations from each other. A motor imagery task can be performed both visually and off, kinesthetic, and open, or vice versa (McInnes, Friesen, & Boe, 2016). However, motor imagery tasks used in neurorehabilitation are mostly explicit motor imagery, utilizing both kinesthetic and visual motor imagery (McInnes et al., 2016).
 |
| C.2 | 
RATIONALE/PURPOSE OF STUDY
 
Most of the studies on motor imagery attribute its mechanism of action to neuroplastic changes occurring in the brain (Gerardin et al., 2000; Kraeutner et al., 2014; Mulder, 2007; Schieber, 2013). On the other hand, it is thought that motor imagery can alter metabolic responses, just like in real exercise. In a study conducted on this subject, it was reported that physiological changes such as heart rate, oxygen consumption, blood pressure, respiratory rate, metabolic rate after motor imaging were like actual exercise (Wang & Morgan, 1992). However, the level of evidence for the effect of motor imagery on autonomic functions is extremely limited.
 
The aims of this study are;
 
 
1. To examine the effects of the activating and relaxing kinesthetic motor imagery training program on autonomic functions in healthy individuals and to compare these two methods with each other.
 
2. In the study, the effects of the mentioned training program on the motor imagery skills of individuals will also be examined.
 
  |

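### For one pre and one post value, ANCOVA with the named contrasts always reported would serve the stated aim better than a mixed ANOVA whose deciding effect is not named

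*Protocol*

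**What the plan says.** Protocol C.3.9 (Statistical analysis) fixes the between-group method for continuous outcomes: "Two-factor mixed pattern analysis of variance (ANOVA) will be used to examine continuous variables such that groups are a factor between participants", with time as the second factor. On effect measures it says "Effect sizes will be calculated as partial eta square values" and names no mean difference or confidence interval. On follow-up: "When a meaningful result is obtained in the relevant analysis, the reason for the difference will be examined with appropriate post hoc correction methods". The same section plans within-group tests: "The significance of the difference between pre-and post-training data will be analyzed in the dependent group using the t-test / Wilcoxon signed-rank test". It sets a two-sided 5% level and analyses participants with follow-up data in the groups to which they were assigned.

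Protocol C.2 gives as the first aim to study both imagery programmes and "to compare these two methods with each other". The sample size paragraph of C.3 settles on 15 per group, raised to 18 per group (54 in all) for losses, and calls the study a pilot.

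**The concern.** C.3.9 leaves four weaknesses in the text as written.

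1. **The deciding effect is not named.** A mixed ANOVA yields group, time and group-by-time effects, and C.3.9 does not say which one answers the aim. The group main effect averages the pre-training value with the post-training value. Randomised groups do not differ in expectation before training, so this halves any effect.
2. **A stated aim is conditional.** Activating versus relaxing is examined only after a significant result, with a correction that is not named. In arms of about 15, that result will often not come.
3. **The effect measure is poorly suited to a pilot.** Partial eta squared does not show which programme moved the outcome up or down, or by how much, and it is biased upward in small samples.
4. **Precision is lost.** Change scores usually use the baseline less efficiently than covariate adjustment does.

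At stake is mainly the estimate a pilot should hand on, the activating-minus-relaxing difference and its confidence interval, rather than a confirmatory test.

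**Working it through.** **The plan's own figures.** 15 x 1.20 = 18 per group and 18 x 3 = 54; 63 x 3 = 189. Both totals reproduce. The protocol states no power or precision for the mixed ANOVA.

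**Inputs.** From the protocol: n = 15 completers per arm (N = 45), three arms, two time points, two-sided 5%. Assumed, because the protocol gives neither: equal pre and post SDs (set to 1) and a pre-post correlation rho, shown over a range.

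**Variance of a group contrast.** Per person:
- change score: 2(1 - rho)
- ANCOVA: 1 - rho^2, times a finite-sample factor 1 + 1/(N - 5) = 1 + 1/40 = 1.025

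The ratio is therefore 1.025 x (1 + rho)/2:

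| rho | (1 + rho)/2 | x 1.025 | Change in variance |
|---|---|---|---|
| 0.5 | 0.750 | 0.769 | -23% |
| 0.7 | 0.850 | 0.871 | -13% |
| 0.9 | 0.950 | 0.974 | -3% |
| 0.95 | 0.975 | 0.999 | 0% |
| 0.98 | 0.990 | 1.015 | +1.5% |

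**95% CI half-width for a pairwise difference**, t x sqrt(variance x 2/15), in SD units, with 42 error df for change and 41 for ANCOVA:
- rho 0.5: change 2.018 x sqrt(1.000 x 2/15) = 0.74; ANCOVA 2.020 x sqrt(0.769 x 2/15) = 0.65
- rho 0.7: 0.57 against 0.53
- rho 0.9: 0.33 against 0.33

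**Which effect is read.** Illustrative post means: activating +0.4, relaxing -0.4, control 0 SD. The F noncentrality is 15 x (sum of squared effects)/variance.
- Interaction: 15 x 0.32/1.0 = 4.8 at rho 0.5 and 15 x 0.32/0.6 = 8.0 at rho 0.7. Power 46% and 68%.
- Group main effect: effects halve to +0.2 and -0.2, and the variance of the pre-post mean is (1 + rho)/2. This gives 15 x 0.08/0.75 = 1.6 and 15 x 0.08/0.85 = 1.4. Power 18% and 16%.
- ANCOVA F: 4.8/0.769 = 6.2 and 4.8/0.523 = 9.2. Power 57% and 75%.

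**The condition on follow-up.** Even if the interaction is the effect read, it misses significance in 100 - 46 = 54% (rho 0.5) or 100 - 68 = 32% (rho 0.7) of such trials. The plan then promises no activating-versus-relaxing comparison.

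**Activating minus relaxing, like for like.** True difference 0.8 SD, Bonferroni for three contrasts (two-sided 0.05/3, critical t about 2.49 to 2.50):

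| rho | Noncentrality, change | Noncentrality, ANCOVA | Power, change | Power, ANCOVA |
|---|---|---|---|---|
| 0.5 | 0.8/0.365 = 2.19 | 0.8/0.320 = 2.50 | 39% | 51% |
| 0.7 | 0.8/0.283 = 2.83 | 0.8/0.264 = 3.03 | 63% | 70% |

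**Partial eta squared under no effect.** With 2 and 42 df it follows a Beta(1, 21) distribution: mean 1/22 = 0.045, 95th percentile 0.133.

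**The case against.** A mixed ANOVA is a standard, valid analysis of a randomised pre-post design, and most analysts would read its interaction without being told. Group means and pairwise differences come from the same fit. C.3.9 mentions Bonferroni, and naming partial eta squared does not forbid a mean difference with its interval. Contrast and interval reporting is often left to a statistical analysis plan. All of this stands, and it makes the point an improvement rather than an error. It does not remove the point, because C.3.9 itself fixes the model, the effect measure and the condition on follow-up.

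A reader might infer more than the documents support:
- **That the baseline is wasted, or that no usable estimate exists.** The interaction uses the baseline through the change score, and the estimates can be obtained; the plan simply does not promise them.
- **That ANCOVA is free.** It costs a degree of freedom and gains nothing near rho 0.95. Adding age and gender as well gives a factor of about 1 + 3/38 if they are not prognostic; at rho 0.9 the variance ratio is then 0.95 x 1.079 = 1.025, slightly worse than change scores.
- **That power leaps from 46%/68% to about 70%/85%.** That sets an omnibus test beside a single contrast with no multiplicity control. The like-for-like gain is 51 - 39 = 12 points at rho 0.5 and 70 - 63 = 7 points at rho 0.7.
- **That partial eta squared will size the full study.** No section says so. C.3 derives 63 per group from heart rate means and SDs in a previous study.

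**Conclusion.** The point holds as a low-cost improvement. C.3.9 leaves the deciding effect unnamed, makes a stated aim conditional on significance, and names only an effect measure without direction or unit. None of these three depends on rho. The precision gain does: a contrast variance about 23% lower at rho 0.5, 13% at 0.7, 3% at 0.9 and nil at 0.95, with 15 per arm and the pre value as sole covariate. The power figures hold only for the illustrative means.

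The argument for ANCOVA also rests on randomisation. The Randomization paragraph of C.3 and section C.3.8 describe random assignment, whereas C.3.5 says Groups 2 and 3 will be matched to Group 1 on age, gender and dominant hand. Those statements need reconciling. Because this is a pilot, the consequence falls mainly on the estimates and their intervals.

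**What to change.** Amend C.3.9 as follows.

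- For each continuous outcome, fit ANCOVA of the post-training value on group and pre-training value. Add age and gender only if judged prognostic, or if the matching in C.3.5 is kept; reconcile C.3.5 with C.3 and C.3.8.
- Report three contrasts whatever the omnibus result: activating minus relaxing, activating minus control, and relaxing minus control. Give each as an adjusted mean difference with 95% CI and a Holm-adjusted p-value.
- Keep partial eta squared as a supplement only.
- Report the SD and the pre-post correlation of each outcome for planning the full study.
- If the mixed ANOVA is retained, name the group-by-time interaction as the effect that answers the aim, and still report the three contrasts unconditionally.

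The cost is a few sentences of wording. The model is available in SPSS and uses the same participants and data. Statistically it spends one error degree of freedom and inflates variance by about 2.5% at N = 45, with no gain if rho is about 0.95 or higher.

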| C.3.5    | 
CONTROL GROUP
 
Participants to be included in Group 2 and Group 3 will be matched by age, gender and dominant hand with those in Group 1.
                                                                                                                                                                                                                                           |                                     |
| C.3.6    | 
THE PLACE THE RESEARCH WILL BE CONDUCTED AND PERMISSIONS
 
The research will be done in the laboratory of Izmir Katip Celebi University Faculty of Health Sciences, Physiotherapy and Rehabilitation under the permission of the Head.
                                                                                                                                               |                                     |
| C.3.7    | 
DATA COLLECTION TOOLS AND FEATURES
 
Dominant hand preference
                                                                                                                                                                                                                                                                                                                 |                                     |

The Edinburgh Handedness Questionnaire (Oldfield, 1971) will be used to determine the dominant hand preference. In this questionnaire, hand preference used in different activities is questioned. The Turkish version of the questionnaire has been shown to be valid and reliable (Nalcaci, Kalaycioglu, Gunes, & Cicek, 2002).

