| C.3.8 | 
OPERATIONS AND VARIABLES TO BE USED IN THE RESEARCH
 
In this study, participants will be randomly assigned to one of three groups: Group 1: activating kinesthetic motor imagery training; group 2: relaxing kinesthetic motor
                                                                                                                                                                                                                                                                                                                                                                                                                                                                                                                                                                                                                                                                                                                                                                                                                                                                                                                                                                                                                                                                                                                                                                                                                                                                                                                                                                                                                                                                                                                                                                                                                                                                                                                                                                                                                                                                                                                                                                                                                                                                                                                                                                                                                                                                                                                                                                                            |

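### C.3.5 matches the groups on age, gender and dominant hand, but the C.3.9 ANOVA omits these factors; if balancing is kept and they are prognostic, between-group power is lost

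*Protocol*

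**What the plan says.** Three places in the protocol bear on this.

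- The section on the control group (C.3.5) states: "Participants to be included in Group 2 and Group 3 will be matched by age, gender and dominant hand with those in Group 1". It gives no matched sets, ratio, age tolerance or procedure.
- C.3, Randomization paragraph: "Participants will be divided into three groups using a simple randomization method based on a single sequence using computer software". C.3.8 repeats that "participants will be randomly assigned to one of three groups". Neither mentions pairs, blocks or strata.
- C.3.9 (Statistical analysis): "Two-factor mixed pattern analysis of variance (ANOVA) will be used to examine continuous variables such that groups are a factor between participants". Time is the within-participant factor, and post hoc comparisons follow a significant result. Age, gender, dominant hand and matched set do not appear in the model. Within each group, pre and post values are compared by paired t-test or Wilcoxon signed-rank test.

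**The concern.** When groups are made alike on a factor that predicts the outcome, that factor no longer contributes to differences between group means. An ANOVA that omits the factor still carries its contribution in the between-participant error term. The error term is then too large for the contrast being tested: the real error rate falls below the stated 0.05, confidence intervals for group differences are too wide, and power is lost.

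C.3.9 names its model and factors, and they do not include the factors that C.3.5 says were used to make the groups comparable. Correcting the allocation text towards strata or matching without changing C.3.9 would leave this mismatch in place.

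**Working it through.** **Inputs from the protocol.** Three groups; 15 per group before allowance for losses; two assessments; two-sided 0.05. The protocol's totals reproduce: 15 × 1.2 = 18 per group, and 18 × 3 = 54. It states no power for the pilot, so there is no power figure to reproduce.

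**Assumptions.** R², the share of outcome variance explained by the three factors, is not given and is varied from 0 to 0.3. The effect is d SD in one group only, with d = 0.5 or 0.8. Balance is taken as exact; looser balance gives smaller losses.

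**Step 1: the test.** With two time points, the group-by-time test is a one-way ANOVA on each person's change, with 2 and 45 − 3 = 42 degrees of freedom and critical value 3.22. The same algebra applies to a comparison of levels; only R² differs.

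**Step 2: independent groups.** The noncentrality is λ = n × d² × 2/3. For d = 0.5, λ = 15 × 0.25 × 2/3 = 2.5 and power is 25.7%. For d = 0.8, λ = 15 × 0.64 × 2/3 = 6.4 and power is 58.1%.

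**Step 3: balanced groups, factors ignored.** Differences between means vary by only (1 − R²) of the usual amount, but the error term stays at the full variance. To a close approximation, the test rejects when an F variable with noncentrality λ/(1 − R²) exceeds 3.22/(1 − R²). At R² = 0.3 the threshold is 3.22/0.7 = 4.60 and the null rejection rate is 1.6%.

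**Step 4: balanced groups, factors as covariates.** The noncentrality is λ/(1 − R²) with 2 and 42 − 3 = 39 degrees of freedom and critical value 3.24. At R² = 0.3 and d = 0.5, λ = 2.5/0.7 = 3.57 and power is 35%.

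| R² | True error, unadjusted | Power at d = 0.5, unadjusted → adjusted | Power at d = 0.8, unadjusted → adjusted |
|---|---|---|---|
| 0 | 5.0% | 26% → 26% | 58% → 58% |
| 0.05 | 4.3% | 25% → 27% | 58% → 60% |
| 0.10 | 3.7% | 24% → 28% | 58% → 63% |
| 0.30 | 1.6% | 19% → 35% | 57% → 74% |

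A simulation with three covariates matched across groups (8,000 runs per setting, prognostic weight on age and gender) gave power gains at d = 0.5 of 2.1, 4.3 and 14.6 points at R² 0.05, 0.10 and 0.30. The adjusted test stayed near 5% under the null at these three values.

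**Step 5: simple randomisation.** In the same simulation with unmatched groups, the unadjusted test rejected at about 5% under the null for every R². Adjusting for three factors with no prognostic value lowered power from 25.6% to 24.1% (d = 0.5) and from 57.3% to 53.9% (d = 0.8). At R² = 0.3, adjustment raised it from 25.2% to 32.6% and from 57.6% to 71.3%.

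**Step 6: which R² applies.** A stable contribution of age, gender or handedness to resting metabolic rate, VO2, VCO2 or VE cancels from a person's change. For the group-by-time contrast, R² is therefore the share of *change* that these factors predict, which is plausibly low. For comparisons of level, such as the group main effect, it may be larger.

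**The case against.** The strongest objection is that simple randomisation from a single sequence is the only allocation procedure the protocol describes. Under it the groups are independent, the mixed ANOVA holds its 5% level, and no power is lost through ignored matching. This stands, and it is why the point is conditional. A reader might infer from C.3.5 that power is definitely lost, but the documents do not support that: one sentence without sets or procedure does not establish that matching will happen.

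Second, the training question is the group-by-time interaction, where stable effects cancel. This also stands. Large losses, such as those at a within-set correlation of 0.5, are arithmetically possible, but no figure in the protocol points to them, least of all for change. What remains is that C.3.9 does not restrict inference to the interaction, and a mixed ANOVA also tests the group main effect.

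Third, a reader might infer that the pilot would hand an inflated variance to the full-scale trial. It would not. Members of one group come from different sets, so the within-group mean square estimates the ordinary variance. That is the right quantity for sizing an unadjusted full-scale trial.

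Fourth, this is a pilot sized by rule of thumb with feasibility criteria, any error is conservative, and covariate lists are often left to an analysis plan. This limits the weight of the point but does not remove it, because C.3.9 itself names the model while C.3.5 names balancing factors that the model leaves out. The within-group pre-post tests are unaffected.

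**Conclusion.** The point holds conditionally. C.3.5 contradicts the Randomization paragraph and C.3.8, and the C.3.9 model takes no account of the factors that C.3.5 says are balanced. The loss arises only if balancing is kept in some form and the factors predict the outcome being compared. The sizes in the table rest on assumed R², exact balance, 15 evaluable per group and an effect in one group only. For the group-by-time contrast the lower rows of R² (0 to 0.10) are the more plausible, which means a loss of roughly 0 to 4 points at d = 0.5. No false-positive risk arises, and no stated power figure is overturned. It is a cheap improvement worth making together with the correction of the allocation text.

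**What to change.** 1. Reconcile C.3.5 with the Randomization paragraph and C.3.8: state whether allocation is simple, stratified or in matched sets.
2. If balancing is kept, add one sentence to C.3.9: the factors used to balance the groups (age, gender, dominant hand) enter all between-group models and post hoc contrasts as covariates. For the group-by-time contrast they must also enter with time, or equivalently as covariates in a model of change; a covariate main effect alone adjusts only comparisons of level.
3. If matching is dropped, delete the C.3.5 sentence. The unadjusted ANOVA is then valid and adjustment is optional.

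Covariates are preferable to a matched-set term: a dropout does not discard the rest of its set, and the adjusted model is valid under either allocation.

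Cost: handedness is already measured under C.3.7, and age and gender are needed for any matching. The model gives up to 3 of about 42 residual degrees of freedom. There is no material power loss if groups are balanced, and a loss of about 2 to 4 points if they are simply randomised and the factors have no prognostic value.
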